### 2.11. Control Variables and Other Parameters to Be Recorded

Different variables will be recorded that may influence the study results, such as (1) sex, age, educational level, marital status, occupational status, the place of living (a city or the countryside); (2) type of cancer; (3) type of cancer treatment (surgery, chemotherapy, immunotherapy, targeted therapy, radiotherapy, or other); and (4) current treatment status (before, during or after the treatment).

### 2.12. Interventions

The Onco-Move exercise intervention is planned according to the CERT. The programme is based on the Individualized and Progressive Health Model [36] (presented in Figure 3.: Onco-Move Individualized and Progressive Health Model) and will include different types of exercises covering all the fitness components (cardio, strengthening, balance, shaping exercises, and stretching). The Individualized and Progressive Health Model (IPS) is a conceptual framework described in a technical monograph [36] and grounded in established exercise prescription principles widely supported by peer-reviewed exercise oncology guidelines.

Participants will perform exercises without any equipment, whereas specific exercises will be performed with such equipment as sports rubber bands, sensory-motor discs, Pilates balls, dumbbells, and cycle ergometers.

All training sessions will be conducted in fitness studios and the gym at Gdansk University of Physical Education and Sport by four certified professional fitness instructors, who will be additionally trained by a certified cancer exercise specialist, and the entire exercise program will be supervised by an expert exercise physiologist with experience in exercise interventions. The in-person interventions will be provided to a group of 20 participants.

The instructors who will supervise exercise performance will correct exercise techniques, ensure the participants maintain the correct movement pattern, provide guidance, provide feedback, and modify exercises as required by a specific type of cancer and treatment.

Adherence will be measured by the percentage of the Onco-Move training sessions completed, defined as the number of the training sessions attended divided by the total number of the training sessions delivered. The reason for absence from training (caused by the treatment regimen, side-effects of treatment, infections, and other reasons) will be reported by patients completing the post-training assessment form (an online tool created by the research team on the Google Forms platform). This approach will allow for feasibility to be evaluated under real-world conditions and provides critical information on barriers that cannot be fully eliminated within the scope of the current study.

Participants who take part in the training will report on the post-training assessment form the extent to which the training affects their general wellbeing. Online post-training assessment forms will be intentionally brief, mobile-friendly, and designed to be completed within a short time frame to reduce participant burden.

Several motivational and social support strategies will be embedded in the Onco-Move intervention. A dedicated WhatsApp group will serve as the primary communication platform to provide timely updates regarding training sessions, assessments, and organizational matters, as well as motivational messages and reminders. This channel will also facilitate peer interaction and social support to enhance adherence in supervised exercise programmes for PLWBC. To strengthen group cohesion and accountability, team-building elements will be incorporated, including group photos, short motivational videos documenting progress, and collective celebration of milestones and seasonal events (e.g., holidays). These activities will be intended to foster a sense of belonging and shared commitment, which may help mitigate dropout risk in a demanding programme.

With respect to logistical burden, training sessions will be scheduled at fixed and predictable time slots to support routine formation while maintaining limited flexibility, when possible, to accommodate treatment schedules and fatigue. All training sessions and assessments will be conducted at a single, familiar location, thereby minimizing logistical complexity and travel-related burden.

Supplementary Materials are provided in Table S2, with a comprehensive description of the Onco-Move exercise programme comprehensive table with photographs for each exercise, videos on the exercises available on https://onkotrening.pl/onco-move-exercise-programme/ (accessed on 13 October 2025), and the list of equipment in Table S3.

Briefly, the training sessions will be conducted in a large enough fitness studio, where each participant will have enough space to exercise. Those participants who report balance issues will be supported by chairs.

The programme will take place three times a week for 16 weeks. Each session will last 45–60 min (fitness and strength training: 10’ warm-up, 40’ training, 10’ stretching, and interval indoor cycling: 10’ warm-up, 25’ training, 10’ stretching).

The exercise programme will be generic for all PLWBC participants and will follow the Exercise Guidelines for Cancer Survivors from the American College of Sports Medicine [5]. However, fitness instructors will be able to modify the exercise prescription based on the patient’s response to the exercise, type of cancer, and treatment and side-effects related to them. Exercise intensity prescription and progression will be primarily based on peak heart rate obtained during cardiopulmonary exercise testing. Given the potential limitations of threshold determination and VO_2_ max assessment in deconditioned cancer populations, training intensity will be individualized using heart rate reserve (HRR), calculated according to the Karvonen method. Target training zones will be expressed as percentages of HRR and progressively adjusted throughout the intervention period according to predefined progression ranges, participant tolerance, perceived exertion, and clinical status.

All adverse events related to the project, intervention, and study measurements will be recorded.

The four fitness instructors will attend a five-hour training session covering knowledge about cancer types, treatment, possible side-effects, and delivery of the Onco-Move exercise programme. Monthly meetings will be held to discuss issues experienced during the training sessions, and solutions will be suggested.

Before the project starts, a risk analysis will be carried out in accordance with the methodology of the Project Management Institute. An impact-probability matrix will be created to identify the project’s most serious risks and conduct a qualitative risk analysis. The most serious risks identified are participant dropout from the Onco-Move programme for health or other reasons and participant safety—procedures to follow should a patient sustain an injury while participating in the proposed training programme. Appropriate risk management strategies will be applied to minimize these risks.

Participant safety will be ensured at multiple levels. First, all participants will be required to obtain written approval from their oncologist prior to enrolment. Baseline functional assessments will be conducted before participation, and exercise prescriptions will be progressively adapted according to participants’ clinical status, treatment phase, and observed tolerance.

During all supervised training sessions, participants will be continuously monitored by certified fitness instructors. Clear criteria for temporary exercise cessation will be applied, including, but not limited to, chest pain, dizziness, excessive dyspnoea, abnormal fatigue, nausea, musculoskeletal pain, or any symptom perceived as alarming by the participant or instructor. In such cases, exercise will be immediately stopped, vital signs will be assessed, and the participant will be referred for medical evaluation when indicated.

Criteria for discontinuation from the intervention will include medical contraindications identified by the treating physician, significant worsening of clinical status, serious adverse events related to exercise, or participant withdrawal of consent. All adverse events will be documented and classified according to severity and relatedness to the intervention.

Importantly, as this study is designed as a feasibility-oriented RCT, safety outcomes (including adverse events, reasons for missed sessions, temporary exercise interruption, and withdrawal) will be treated as key feasibility indicators. These data will inform the refinement of safety protocols and stopping rules in subsequent larger-scale trials.

### 2.13. Data Collection, Management, and Analysis

On the day of the first measurements at the Physical Exercise Laboratory at GUPES, project participants will be given individual codes according to the scheme n/01/OM, where n means the participant’s consecutive number, 01—first edition, and OM—Onco-Move program. Data typical for each of the research tasks will be collected in Excel spreadsheets. These data will be successively entered into a collective electronic database. Standardized coding of participants will enable easy linking of databases, including, e.g., performance test results and their multiple use.

The data will be stored in the form of Excel and Statistic electronic spreadsheets, Word documents of measurements, and recordings of exercise sessions (jpg, tiff, mp4 format). The data will be also stored in paper form. Data in paper form will be collected in an amount proportional to the number of project participants and stored in properly described binders. Documents will be classified and described according to the procedures adopted by GUPES.

Moreover, the consent form for participation will be distributed to all participants and signed.

Personal and sensitive data will be secured in accordance with the regulations in force at GUPES, with particular attention to data safety. Personal data will be processed and protected in accordance with the Act of 10 May 2018 on the protection of personal data and the guidelines applicable at GUPES.

### 2.14. Statistical Analysis

Descriptive statistics will summarize baseline characteristics. Primary analyses will follow the intention-to-treat (ITT) principle. To evaluate changes across time points (baseline, 8 weeks, 16 weeks, follow-up), a mixed-effects model for repeated measures (MMRM) will be applied with random intercepts for participants and fixed effects for group, time, and group × time interaction, adjusting for relevant covariates (baseline value, age, sex, treatment status). A covariance structure such as compound symmetry or AR(1) will be selected based on model fit.

For outcomes with only two time points or in case of convergence limitations due to sample size, ANCOVA models adjusted for baseline values will be used as a complementary approach. Effect sizes (Hedges’ g) and 95% confidence intervals will be reported to prioritize estimation over strict hypothesis testing, in line with the feasibility nature of the study. Missing data will be handled using maximum likelihood estimation within the mixed-model framework, and complete-case or multiple-imputation sensitivity analyses will be performed when appropriate. Exploratory moderator analyses (e.g., treatment status, cancer type, adherence) will be reported descriptively. Data will be analyzed using IBM SPSS Statistics (version 29) and Stata (version 18). All tests will be two-sided with α = 0.05.

Given the pilot and feasibility-oriented nature of the study, formal correction for multiple comparisons is not planned. Secondary and exploratory outcomes will be interpreted with caution, emphasizing estimation, variability, and hypothesis generation rather than confirmatory statistical inference.

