### 2.6. Sample Size

The study was pragmatically powered with n = 20 participants per group (intervention and control) for this initial feasibility and estimation phase. The calculation assumes a two-sided α = 0.05 and a nominal power of 80%, using an ANCOVA model adjusted for baseline values and repeated measures to increase statistical efficiency. Previous exercise-based trials in PLWBC [14,15,16] have reported between-group differences of approximately 8–10 points in the EORTC QLQ-C30 Global Health Status/QoL domain, with standard deviations around 20–30 points. Based on these data, a fully powered confirmatory trial would require substantially larger samples; therefore, the present study adopts a realistic initial sample size aimed at (i) quantifying the signal of efficacy and its heterogeneity across subgroups, (ii) evaluating feasibility, adherence, and safety, and (iii) providing empirical estimates of variance, correlation, and attrition rates to inform a subsequent definitive trial with higher precision. Should recruitment capacity allow, the sample may be progressively expanded to narrow confidence intervals around clinically meaningful differences of 8–10 points.

Furthermore, feasibility expectations regarding adherence and dropout are informed by a previous pilot study conducted in 2023 at GUPES. Based on this experience, we anticipate an adherence rate of approximately 60–70% in the current RCT, with an expected dropout rate of around 25%. Dropout is primarily anticipated among participants undergoing active cancer treatment, who may experience treatment-related side-effects or changes in medical status that prevent continued participation.

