### 2.9. Assessment Protocol

Each patient who participates in the project will undergo four assessments over the course of the project: (1) a baseline assessment—before participating in the Onco-Move training programme; (2) 8 weeks after the programme begins; (3) 16 weeks after the programme begins; (4) 3 months after the completion of the Onco-Move intervention.

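### The primary mixed model uses the baseline score both as a response and as a covariate, so the week-16 standard error is too small or the baseline adjustment is lost, depending on an unnamed contrast

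*Protocol article*

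**What the plan says.** Section 2.14 of the protocol article sets out the primary model: "To evaluate changes across time points (baseline, 8 weeks, 16 weeks, follow-up), a mixed-effects model for repeated measures (MMRM) will be applied". The same sentence adds a random effect, "with random intercepts for participants", and then "fixed effects for group, time, and group × time interaction, adjusting for relevant covariates (baseline value, age, sex, treatment status"). The next sentence reads: "A covariance structure such as compound symmetry or AR(1) will be selected based on model fit". Nothing in the section removes baseline from the responses, constrains the arms to a common baseline mean, or says which group contrast is the treatment effect.

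If the model does not converge, or an outcome has only two time points, "ANCOVA models adjusted for baseline values will be used as a complementary approach".

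Section 2.6 describes the study as "pragmatically powered with n = 20 participants per group (intervention and control") and continues: "The calculation assumes a two-sided α = 0.05 and a nominal power of 80%, using an ANCOVA model adjusted for baseline values and repeated measures". The stated reason is statistical efficiency. Section 2.9 places the last assessment at "4) 3 months after the completion of the Onco-Move intervention", which is about week 29 if three months are taken as 13 weeks.

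**The concern.** If baseline is a row of the response vector and also a covariate, then at that row the outcome equals its own predictor. One common slope for baseline is fitted across all four rows. The baseline row pulls that slope towards 1 and leaves almost nothing unexplained there, so the model underestimates how much participants differ after adjustment.

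Two results could be read off the fitted model as the treatment effect:

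- the adjusted group difference at a post-baseline visit, which inherits the understated variance;
- the group-by-time contrast against baseline, in which a covariate that is constant within a participant cancels, so it is not baseline-adjusted at all.

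Health-related quality of life is the sole primary outcome. The article says that it puts estimation and confidence intervals first and that the pilot will supply variance and correlation estimates for a definitive trial. Those are the quantities affected.

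A second, separate matter is that a random intercept is already a compound-symmetry model. Adding a compound-symmetry residual enters the same parameter twice.

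**Working it through.** **Inputs.** From the article: 20 per arm, two-sided α 0.05, differences of 8–10 points, SD 20–30, dropout about 25% (section 2.6); four visits (section 2.9). Assumed, because the article gives no value: between-visit correlation ρ from 0.3 to 0.7 with compound symmetry, and SD σ = 25, the midpoint of 20–30. The SE ratios below do not depend on σ.

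**The plan's own figure.** The nominal 80% power is not reproduced from 20 per arm. Unadjusted, the stated differences and SDs need 63 to 221 per arm, and 20 per arm gives 13–35% power. The article concedes that a fully powered trial would be much larger. That is not the point here; what matters is that section 2.6 relies on baseline-adjusted ANCOVA.

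**(a) Adjusted group difference at week 16, model as written, complete data.** The covariate is constant within a participant, so its slope comes from the participant means over four visits:

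- Slope: β = (1+3ρ)/4.
- True variance of the adjusted week-16 value, in units of σ²: 1 + β² − 2βρ.
- Random-intercept variance that the model fits: τ² = β − β² − (1−ρ)/4.
- Variance that the model assumes: τ² + (1−ρ).

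| ρ | β | True variance | τ² | Assumed variance | SE ratio |
|---|---|---|---|---|---|
| 0.3 | 0.475 | 0.941 | 0.074 | 0.774 | 0.91 |
| 0.5 | 0.625 | 0.766 | 0.109 | 0.609 | 0.89 |
| 0.7 | 0.775 | 0.516 | 0.099 | 0.399 | 0.88 |

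At ρ = 0.5 the model SE is 25·√(0.1 × 0.609) = 6.17, against a true 25·√(0.1 × 0.766) = 6.92. A correctly adjusted model would have a random-intercept variance of ρ − ρ² = 0.25σ², not 0.109σ².

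Simulations under no effect agree:

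- Closed-form REML, 20,000 trials per ρ: SE ratio 0.89–0.90; type I error 6.9–7.8% (t reference) or 7.9–8.9% (z). ANCOVA on the same data gave 4.9–5.5%.
- Iterative REML/GLS, 1,000 trials per scenario, including a decaying correlation: ratio 0.91–0.94, type I error 6.3–7.6%. At ρ = 0.5 the correct post-baseline model in this set had a ratio of 6.86/6.65 = 1.03, so the simulated spread ran slightly low, which explains part of the gap from the formula.
- 25% dropout completely at random, ρ = 0.5: ratio 0.84, type I error 9.8%. The two corrected models gave 5.7% and 5.3%.

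**(b) Group-by-time contrast against baseline.** The covariate cancels, leaving the raw change score. Its variance factor is 2(1−ρ), against 1−ρ² for ANCOVA, a ratio of 2/(1+ρ). The SE excess is therefore √(2/1.3) − 1 = 24%, √(2/1.5) − 1 = 15% and √(2/1.7) − 1 = 8% at ρ = 0.3, 0.5 and 0.7. Simulated model SEs were 9.34 against 7.57 (23%), 7.90 against 6.87 (15%) and 6.12 against 5.66 (8%). Type I error at ρ = 0.5 was 4.1%, so the contrast is valid. At ρ = 0.5 and SD 25, power for 10 points falls from 28% with ANCOVA to 23%.

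**(c) Covariance.** A random intercept with variance τ² plus a compound-symmetry residual with common covariance c gives a between-visit covariance of τ² + c. The data identify only the sum. Random intercept alone and compound symmetry alone gave the same fixed-effect SEs, so the stacking does not cause the error in (a). Random intercept plus AR(1) is identifiable with four visits. In 250 runs it showed the SE error less strongly: for the mean of the post-baseline visits the ratio was 0.87–0.89, against 0.84 for the random intercept alone. AR(1) by visit number treats gaps of 8, 8 and about 13 weeks as equal.

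**Limits.** Age, sex and treatment status were left out of the simulations, and degrees of freedom were approximate.

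**The case against.** The strongest reply is that the list of time points may only describe the assessment schedule. Naming baseline as a covariate, together with the ANCOVA language of section 2.6, would also fit a model with post-baseline responses only. The article is condensed, and the make-up of the response vector is often settled in an analysis plan. This carries some weight, since the article never says outright that baseline is a response row. Even so, baseline is named among the times the model covers, in the same sentence that names it as a covariate, so the text as printed specifies both uses.

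A second reply is that an aim of evaluating change with a group-by-time term points to the contrast against baseline, whose type I error is correct. That stands too, and it is why the inflation is conditional. It does not rescue the plan, because that contrast gives up the adjustment on which section 2.6 relies.

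Some stronger inferences are not supported:

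- **The random intercept makes the standard errors wrong.** It does not; the error comes from using baseline twice.
- **The treatment estimate is biased.** No material bias appeared.
- **Choosing the covariance structure by model fit is a defect.** It is a declared and common rule, and the structures are named only as examples.
- **The ANCOVA fallback simply discards participants.** The article also provides for multiple-imputation sensitivity analyses.

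**Conclusion.** The point holds in conditional form. As printed, the primary model uses baseline twice, and the consequence follows from a contrast that the article does not name:

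- **Adjusted difference at week 16:** SE about 6–12% too small and type I error about 6–8% (t reference) with complete data and ρ 0.3–0.7; about 10% with 25% dropout at ρ = 0.5.
- **Group-by-time contrast against baseline:** valid, but with an SE about 8–23% larger than ANCOVA's as ρ goes from 0.7 to 0.3.

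These sizes rest on an assumed correlation and on compound symmetry. A reader might infer that the primary result is bound to be anti-conservative; the documents do not support that, because the contrast is left open. The random intercept with a compound-symmetry residual is a separate fitting problem. It is likely to produce convergence warnings, and non-convergence is the article's own trigger for ANCOVA.

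This should be fixed rather than treated as fatal. The trial is a 40-person estimation pilot and concedes that it is not fully powered, but its confidence intervals and variance estimates are among its stated products.

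**What to change.** Rewrite the model description in section 2.14 in one of two ways:

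1. Use weeks 8, 16 and follow-up as the responses, with baseline and baseline-by-visit as covariates, alongside group, visit, group-by-visit, age, sex and treatment status.
2. Keep baseline as a response, constrain the arms to a common baseline mean, and drop the baseline covariate.

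In either case, use a single source of within-person covariance, with no random intercept on top of compound symmetry. If AR(1) stays a candidate, note that the visits are unequally spaced. State which group contrast, at which visit or average of visits, is the primary quality-of-life effect. The covariance structure and degrees-of-freedom method can be left to the trial statistician.

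The cost is analysis wording only. No extra participants, visits or data are needed.

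### The mixed-model sentence names only maximum likelihood; read literally, it gives week-16 standard errors about 6–7% below REML in this 40-person trial, and a one-sentence change removes the risk

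*Protocol article*

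**What the plan says.** Section 2.14 (Statistical Analysis) sets out a repeated-measures mixed model with random intercepts, group, time and their interaction, adjusted for baseline value, age, sex and treatment status. On estimation it says only that "Missing data will be handled using maximum likelihood estimation within the mixed-model framework", followed by complete-case or multiple-imputation sensitivity analyses. It does not mention REML, a degrees-of-freedom method or a reference distribution. ANCOVA is kept for outcomes measured twice and for convergence problems.

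The same section says that "95% confidence intervals will be reported to prioritize estimation over strict hypothesis testing", and also that "All tests will be two-sided with α = 0.05". Section 2.6 (Sample Size) fixes 20 participants per group, expects dropout of around 25%, and lists among the trial's purposes "providing empirical estimates of variance, correlation, and attrition rates to inform a subsequent definitive trial with higher precision".

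**The concern.** Full ML estimates variance components as though the fixed effects were known. With hundreds of participants this does not matter. With 40 participants and about 10 coefficients, the variance estimate is biased downwards, and standard errors and intervals shrink with it. Normal critical values would narrow the intervals further.

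REML deducts the fitted coefficients and handles missing outcomes under the same missing-at-random assumption, so full ML gains nothing on missing data. The interval for quality of life, the sole primary outcome, is the result this pilot says it values most, and its width is what the choice affects.

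**Working it through.** **Inputs from the article.** n = 40, 1:1; dropout about 25%, so 40 × 0.75 = 30 completers; two-sided α = 0.05; model terms as in Section 2.14; treatment status with up to three levels (Section 2.11).

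**Assumed, because the article gives no value.** Correlation between visits 0.5 or 0.7; compound symmetry; random monotone dropout; three post-baseline visits as outcomes, with baseline as covariate only.

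**The plan's own figure.** The sample size of 20 per group can be reproduced only in a corner. Take 10 points, SD 20, correlation 0.7, the mean of three post-baseline visits and no dropout. The variance factor is (1 + 2 × 0.7)/3 − 0.7² = 0.31, and n = 2 × (1.96 + 0.842)² × 0.31 × 20²/10² = 19.5, rounded up to 20. Section 2.6 itself concedes that a fully powered trial needs far more participants, so this does not bear on the estimator. It does show that 0.7 is a relevant correlation to include.

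**Step 1: count the coefficients.** Between participants: intercept, group, baseline, age, sex and treatment status, so k = 6 (7 if treatment status has three levels). Within participants: 2 for time and 2 for group × time. The total is 10 (or 11).

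**Step 2: closed form, balanced data.** For the between-participant part, ML divides by n and REML by n − k, so the standard-error ratio is √((n − k)/n).
- n = 40: √(34/40) = 0.922 and √(33/40) = 0.908. Type I error is 7.0–7.4% (t) or 8.0–8.4% (normal).
- n = 30: √(24/30) = 0.894 and √(23/30) = 0.876. Type I error is 7.7–8.3% (t) or 9.2–10.0% (normal). This is an outer bound, because the mixed model also uses partial data from people who drop out.

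These figures apply to the visit-averaged contrast. The week-16 contrast also uses within-participant variance, which ML understates less: 40 × 2 = 80 degrees of freedom, of which 4 are used, so the ratio is 76/80 = 0.95. Take correlation 0.5 and unit total variance. After baseline adjustment the variance is 1 − 0.25 = 0.75 and the covariance 0.5 − 0.25 = 0.25, so the residual variance is 0.5. The between part of the week-16 variance is (0.5 + 3 × 0.25)/3 = 0.417 and the within part is (2/3) × 0.5 = 0.333. The ML/REML variance ratio is (0.417 × 0.85 + 0.333 × 0.95)/0.75 = 0.894, and the standard-error ratio is √0.894 = 0.946.

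**Step 3: simulation under no effect.** 4,000 trials per row, Monte Carlo error about 0.4 points. The t reference uses participants minus subject-level coefficients as degrees of freedom. Week-16 contrast:

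| Correlation / dropout / fixed effects | SE, ML ÷ REML | ML, normal | ML, t | REML, t |
|---|---|---|---|---|
| 0.5 / 0% / 10 | 0.945 | 7.0% | 6.0% | 4.5% |
| 0.5 / 25% / 10 | 0.936 | 8.0% | 6.9% | 5.1% |
| 0.7 / 0% / 10 | 0.942 | 6.0% | 5.2% | 3.7% |
| 0.7 / 25% / 10 | 0.934 | 7.5% | 6.5% | 5.0% |
| 0.5 / 25% / 11 | 0.927 | 7.2% | 6.1% | 4.4% |

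The first row agrees with the hand calculation (0.945 against 0.946). For the visit-averaged contrast the ranges are 7.6–8.8% (ML, normal), 6.6–8.1% (ML, t) and 4.4–6.0% (REML, t). A separate simulation with 10 fixed effects, correlation 0.5–0.7 and 0–25% dropout gave week-16 standard errors 5.5–6.6% below REML, with type I error 6.6–7.7% (ML, normal), 5.6–6.4% (ML, t) and 3.9–5.0% (REML, t).

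**Step 4: separate the two sources.** In the second row, moving from REML to ML with t critical values adds about 1.8 points (5.05% to 6.88%). Moving from t to normal adds about 1.2 more (6.88% to 8.03%). Only the first part follows from the estimator the article names; the article is silent on the second.

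**The case against.** The strongest reply is that the quoted sentence is about missing data. Its contrast is between likelihood and deletion or imputation, not between ML and REML, and such wording is often used loosely for any likelihood-based analysis, REML included. ML versus REML and degrees of freedom are also details usually left to a statistical analysis plan, which is not at hand. This largely stands. A reader might infer that the plan has chosen full ML and that its tests therefore run above 5%; the text does not support that as fact. The absence of a degrees-of-freedom method is likewise no fault in itself. What remains is that the only estimator named for the primary model is one that a literal reader would implement as full ML.

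A reader might also infer that the definitive trial would be planned too small. Section 2.6 promises variance estimates but does not say they will be ML components. Ordinary group SDs and the ANCOVA models are unaffected. Even for ML components, the sampling error of an SD on 34 to 39 degrees of freedom is 1/√(2 × 34) = 12% to 1/√(2 × 39) = 11%, which is larger than the bias. Nor does naming both SPSS and Stata show that one must be dropped.

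Finally, a pilot that favours estimation would hardly reverse a decision over one to three percentage points. That is fair, and it limits the weight of the point.

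**Conclusion.** The point holds conditionally and is modest: a cheap improvement, not an error. If the sentence is followed as full ML, week-16 standard errors are about 6–7% smaller than under REML. Type I error is about 5–7% with t critical values and 6–8% with normal ones, and nominal 95% intervals cover about 92–95%. The visit-averaged contrast is somewhat worse. The lowest ML result (5.2%) is within simulation error of 5%.

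The result rests on the assumed correlation, compound symmetry and random dropout. AR(1) and choosing the covariance structure by fit, both of which Section 2.14 allows, were not simulated. If baseline were also modelled as an outcome, since Section 2.14 lists it among the time points, there would be 12–13 fixed effects; that was not simulated either.

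**What to change.** Replace the missing-data sentence in Section 2.14 with:

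*The mixed model is fitted by restricted maximum likelihood with a small-sample degrees-of-freedom method (Kenward-Roger or Satterthwaite); missing outcomes are handled under missing at random within this likelihood.*

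Keep the sensitivity analyses as they are, and report the REML variance components as the planning estimates for the definitive trial. If REML was intended all along, the edit only removes a possible misreading. The cost is slightly wider stated intervals. The simulations used a simple subject-level t reference with REML, which came close to 5% (3.7–5.1% at week 16); the two named methods were not themselves simulated.
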